## Abstract

**Background:**

Maintaining independence is a key priority for older adults and a central goal of district nursing care. Although person-centered shared decision-making and the use of routinely collected care data are recognized as strategies to support independence, their combined use in district nursing care has not yet been studied.

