## Background

1

Worldwide, older adults want to stay in their own homes as they age, valuing independence and safety. Although aging often involves multiple chronic conditions and independent functioning related problems, the desire to live independently remains strong (Chowdhury et al., 2023). District nursing care supports the goal of older adults aging in place by making person-centered shared decisions about care and interventions that help maintain daily functioning and delay or prevent institutionalization (Dostálová et al., 2021). The growing number of older adults with complex care needs is placing increasing demands on district nursing care (McGilton et al., 2018). Beyond illness-related care needs, these older adults have specific physical, psychological, and social needs related to maintaining their independent functioning (Ho et al., 2023; Marriott-Statham et al., 2023). This has intensified the need for district nursing interventions that actively support and sustain independence in daily life (Hoffmann et al., 2018).

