In line with the Dutch Health Council, in this study, independent functioning for home-dwelling older adults is described as the capacity to maintain physical, psychological, and social wellbeing, with or without formal or informal care, and to retain control over daily life during a stage marked by inevitable changes and losses (Gezondheidsraad, 2018; Huber et al., 2011). Supporting independent functioning requires two core elements that together form the focus of this study. The first is person-centered shared decision-making, defined as a collaborative process in which healthcare decisions are made jointly by patients, their families, and healthcare professionals, with a primary focus on eliciting and prioritizing personal and care-related goals, and on aligning these goals with interventions (Elwyn and Vermunt, 2020). In contrast to disease-oriented shared decision-making, person-centered shared decision-making typically centres on the person across life domains and uses their fundamental goals, values, and priorities as the basis for care decisions, instead of focusing solely on biomedical abnormalities, the medical management of underlying conditions, or adhering to clinical guidelines designed for single diseases (Elwyn and Vermunt, 2020; Van de Pol et al., 2016). The second is data-informed care, which we define as the structured use of routinely collected patient data, including longitudinal information on functioning, to support clinical reasoning and shared decisions about care (Veldhuizen et al., 2024a; Veldhuizen et al., 2024b).

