### Study setting

3.3

This study will be conducted in the Netherlands as part of the Data Nurse project, titled “Data-informed Essential Care in District Nursing Care: Improving Patient Outcomes and Maintaining Independence”. Four large care organizations that provide district nursing care across the Netherlands, selected to represent both urban and rural areas, will participate. Participants include district nursing team members and older adults aged 65 and older who receive district nursing care.

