### Secondary outcomes

3.15

Secondary outcomes are the preliminary effectiveness of the Data Nurse intervention, assessed in both intervention and control groups.

Self-reported independent functioning will be measured using the selected domains of the TOPICS-SF that assess independent functioning (Santoso et al., 2018), a patient-reported outcome measure assessing health and functioning across multiple domains, including physical health, mental health, social support, and overall wellbeing. In the intervention group, this is measured through the patient preparatory tool shared decision-making, which incorporates the TOPICS-SF items. In the control group, older adults will complete the selected domains of the TOPICS-SF separately. As the instrument is administered through different channels, group comparability will be considered in the analysis.

Patient-reported shared decision-making reflects the level of shared decision-making in the clinical encounter from the older adults' perspective. This will be measured using the CollaboRATE questionnaire (Elwyn et al., 2013), a three-item instrument, scored from 0 to 9, that evaluates the extent to which older adults perceive their concerns to be heard and integrated into care decision-making.

District nursing care delivery patterns will be extracted from electronic nursing record data for both groups, including visit frequency, care delivery mode (in-person, phone, video), use of healthcare technology, and total care hours. Additionally, three data-informed indicators are extracted from the electronic nursing record system to explore the extent to which care activities are aligned with promoting patient independence: (1) the proportion of nursing interventions aimed at promoting independent functioning, as documented in the care plans; (2) the proportion of older adults showing improvement in care need scores between intake assessment and evaluation, or between successive evaluations; and (3) the proportion of older adults who achieved their individually set target scores per care need during the study period.

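### Record-based indicator (2) counts only improved care need scores, so taken alone it cannot tell a stable course from decline, although maintaining independence is the main stated goal

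*Protocol article*

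**What the plan says.** Section 3.15 (Secondary outcomes) lists three indicators taken from the electronic nursing record in both groups. Their stated purpose is "to explore the extent to which care activities are aligned with promoting patient independence". Indicator (2) is "the proportion of older adults showing improvement in care need scores", judged either from intake to evaluation or from one evaluation to the next. Indicator (3) is "the proportion of older adults who achieved their individually set target scores per care need during the study period". Nowhere does the article add a stable, maintained or declined category to indicator (2).

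On the goal, the Abstract opens with "Maintaining independence is a key priority for older adults and a central goal of district nursing care". Section 1 (Background) says that district nursing should "help maintain daily functioning and delay or prevent institutionalization". It defines independent functioning partly as the capacity to "retain control over daily life during a stage marked by inevitable changes and losses". The project title in section 3.3 includes "Improving Patient Outcomes and Maintaining Independence".

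Section 3.13 makes all effectiveness outcomes exploratory and untested, and says that they are to inform a later randomized trial. Section 4.2 plans effect sizes and confidence intervals for the same purpose.

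**The concern.** Under the article's own definition of independent functioning, a person who holds their score over the five months has done well. Indicator (2) places that person in the same class as someone who got worse. An intervention that works by preventing decline would leave no trace on it, and neither would a worsening among people who had been stable.

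The study is meant to help decide whether a larger trial is worthwhile and how to design it. If indicator (2) is carried forward as an outcome or an effect size, a flat result could be read as no effect on independence when the measure could not have shown the effect most often described as the aim. The article itself fixes the direction of change that counts, so this is not a detail left to an analysis plan that is not shown.

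**Working it through.** **The plan's own figure.** The article gives no expected value for indicator (2). The only related figure is the number of older adults, from section 3.17: 14 teams × 30 = 420 eligible; 420 × 0.50 = 210 and 420 × 0.70 = 294. This reproduces the 210–294 in the Abstract. If participation is equal in both groups (an assumption), the groups are:

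- 50% participation: 8 × 30 × 0.50 = 120 intervention, 6 × 30 × 0.50 = 90 control.
- 70% participation: 8 × 30 × 0.70 = 168 intervention, 6 × 30 × 0.70 = 126 control.

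**The logic.** In each group let I, S and D be the proportions improved, stable and declined, with I + S + D = 1. Indicator (2) is I. Maintained or improved is I + S = 1 − D. If a proportion x moves from declined to stable, S becomes S + x and D becomes D − x. I is unchanged, and I + S rises by x. The same holds with the sign reversed. This does not depend on the rates.

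**Illustration (all rates are assumptions; the article gives none).**

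| | Improved | Stable | Declined | Maintained or improved |
|---|---|---|---|---|
| Control | 20% | 50% | 30% | 70% |
| Intervention, decline halved | 20% | 65% | 15% | 85% |
| Intervention, stable people worsen | 20% | 35% | 45% | 55% |

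- Decline halved: indicator (2) gives 20 − 20 = 0 points; maintained or improved gives 85 − 70 = +15 points.
- Stable people worsen: indicator (2) gives 20 − 20 = 0 points; maintained or improved gives 55 − 70 = −15 points.

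**Range.** Set the declined proportion at 20% in the intervention group and at 30%, 40% or 50% in control. Maintained or improved then differs by 10, 20 or 30 points. With I equal in both groups (10%, 20% or 30%), indicator (2) differs by 0 each time.

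**Precision.** Half-width = 1.96 × √[p₁(1 − p₁)/n₁ + p₂(1 − p₂)/n₂], ignoring clustering in 14 teams, so the real intervals would be wider.

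- Indicator (2) at 20% against 20%: 1.96 × √(0.16/120 + 0.16/90) = 10.9 points; with 168 and 126 people, 9.2 points.
- Maintained or improved at 80% against 60%: 20 points, interval 7.6 to 32.4 with 120 and 90 people; 9.5 to 30.5 with 168 and 126.

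**Side effect of the wording.** Because improvement between successive evaluations also counts, a person who declines and then recovers can be counted as a success. A person who never declined cannot.

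**The case against.** The strongest reply has four parts.

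1. *Indicator (2) is not the only measure of functioning.* Self-reported functioning on selected TOPICS-SF domains is measured at baseline and close-out in both groups (Table 1). Section 4.2 describes its change without restricting the direction, so less decline in one group can show there. This stands, but it is partial cover: sections 3.15 and 5.1 warn that the questionnaire reaches the two groups by different routes, which weakens the comparison.
2. *Indicator (3) may credit maintenance.* It does so if a target may equal the current score. The article does not say whether it may. Goal-setting is also part of what the intervention tries to change, so targets may differ between groups.
3. *Improvement is also an aim.* The Abstract's conclusion speaks of enhancing independence, and the project title names both improving outcomes and maintaining independence. This stands: the indicator is relevant but incomplete. It does respond if the intervention moves people from stable to improved.
4. *The zero is built into the example.* This is true of its size, because improvement is held equal by assumption. That movement between stable and declined goes unseen is not an assumption.

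A reader might also infer a ceiling problem, with many participants starting at the best score because section 3.8 excludes severe impairment. The documents do not support this. They give no score distribution, and participants are by definition receiving care. Excluding the most impaired does not show clustering at the top, and a person may have several scored needs.

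**Conclusion.** The point holds for indicator (2) only. As defined, it does not separate a stable course from decline, so taken alone it would register neither prevented decline nor decline in previously stable people. That conclusion needs no assumed rates. The 0 against 15 point contrast is an illustration of the mechanism, not an expected effect.

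Two stronger readings should be resisted. A reader might infer that the study cannot detect prevented decline at all; TOPICS-SF change, and possibly indicator (3), can show it. A reader might also infer that harm would go unnoticed; section 3.16 explores unintended effects through interviews, focus groups and the monthly meetings, so that does not rest on this proportion.

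The weight is modest because the outcome is secondary, exploratory and untested. The change is still worth making because the results are intended to shape a later trial.

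**What to change.** In section 3.15, redefine indicator (2) as the proportions of older adults with an improved, unchanged and declined care need score, by group, from the scores already being extracted. Show maintained or improved (equivalently, declined) beside improved, so that both the maintenance goal and the improvement goal can be read.

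Because one person may improve on one need and decline on another, either tabulate per care need or state a single rule for classifying people with several needs. Say which pair of assessments the classification uses, so that each person falls into one category.

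No new data are collected and participants carry no extra burden. The cost is one aggregation rule and a slightly larger table.

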**Methods:**

The Data Nurse intervention combines two components: (1) person-centered shared decision-making with older adults, supported by a patient preparatory tool shared decision-making, and (2) learning from data via a digital dashboard that visualizes longitudinal independence data from electronic nursing records. In this continuous cycle, interventions to support independent functioning are planned and documented; independence data are visualized and discussed during team reflection sessions, discussed with patients, and interventions to support independent functioning are evaluated and adjusted as needed. Primary outcomes on feasibility, acceptability, fidelity, experiences, barriers and facilitators will be assessed through the validated questionnaires Feasibility of Intervention Measure, the Theoretical Framework of Acceptability questionnaire, the Theoretical Domains Framework, self-developed questionnaires, focus groups, and interviews with patients and district nurses. Fidelity will be monitored through monthly meetings using a self- developed questionnaire. Secondary outcomes on preliminary effectiveness on independent functioning will be measured using selected domains of the TOPIC-SF questionnaire and electronic nursing record data. In addition, patient perceived involvement in the shared decision-making process is measured with the CollaboRATE. Data will be analyzed using descriptive statistics and thematic analysis.

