Second, data in electronic district nursing records is primarily used for documentation purposes rather than to support care decisions (Veldhuizen et al., 2024a). A systematic review of digital health systems in nursing found that while assessment and planning are increasingly captured electronically, the documentation and evaluation of nursing interventions and patient outcomes remain largely absent, limiting nurses' ability to use data for decision-making (Hants et al., 2023). A recent scoping review of shared decision-making tools integrated into electronic health records similarly found that most tools were designed primarily for clinicians, with patient-specific goals and values included in only just over half of the studies and that integration approaches varied widely: from scanned paper documents to fully interoperable tools (Pierce et al., 2025). This is particularly relevant for district nursing care, where care planning must align with older adults' daily lives and long-term needs. Electronic nursing records contain valuable information on care delivery patterns. However, this data is rarely used to monitor longitudinal trends in independent functioning or to inform collaborative decision making with older adults (Siette et al., 2023). The potential of using electronic nursing record data to substantiate and evaluate nursing interventions that support independence thus remains untapped.

While both person-centered shared decision-making and data-informed care are individually recognized as important strategies to enhance care quality and patient independence, their combined implementation in district nursing care has not yet been studied. In response to these knowledge gaps, we developed the Data Nurse intervention, which combines person-centered shared decision-making with data-informed care for supporting older adults' independence. This article describes the protocol for a multicenter feasibility study of the Data Nurse intervention.

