
### The data nurse intervention

3.5

The Data Nurse intervention integrates person-centered shared decision-making with data-informed reflective practice in a continuous cycle in clinical practice. In this cycle, older adults are encouraged and prepared to actively participate in shared decision-making by using the patient shared decision‑making preparatory tool to articulate and reflect on their independence goals, values, and care preferences through structured questions about daily functioning and what matters most to them (Supplementary File 2). Based on this tool, district nurses engage in shared decision-making conversations with older adults about interventions to support their independence. Care decisions and interventions are subsequently documented in the electronic nursing record using the Omaha System classification, generating data on nursing care delivery and patient functioning. This data will be used in the Data Nurse dashboard, visualizing longitudinal trends in patient independence scores across multiple domains (e.g., mobility, self-care, social functioning), frequency and types of nursing interventions aimed at supporting independence, individual patient trajectories, and team-level patterns in care delivery (van den Braak et al., 2026). In regular team reflection sessions, led by trained data, teams will review dashboard insights to identify patterns in the independent functioning of older adults, and evaluate interventions to support independence. These insights into independence will then be shared with older adults during care evaluations. This cycle of decision-making, documentation, visualization, and reflection is intended to close the loop between data and practice, supporting continuous learning and adaptation in daily care in line with the principles of a learning health system (Foley and Vale, 2023).

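### The three record-based indicators in 3.15 are labelled preliminary effectiveness, but the intervention changes how the record is made in one arm only, so a group difference cannot be separated from a change in recording, scoring or target-setting

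*Protocol article*

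**What the plan says.** Section 3.15 opens with "Secondary outcomes are the preliminary effectiveness of the Data Nurse intervention, assessed in both intervention and control groups". Under that label it lists three indicators taken from the electronic nursing record. Indicator (1) is "the proportion of nursing interventions aimed at promoting independent functioning, as documented in the care plans". Indicator (2) is the share of older adults whose care-need scores improve from one assessment to a later one. Indicator (3) is "the proportion of older adults who achieved their individually set target scores per care need during the study period".

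The article describes what these data measure in two ways. The abstract (Methods) states: "Secondary outcomes on preliminary effectiveness on independent functioning will be measured using selected domains of the TOPIC-SF questionnaire and electronic nursing record data". Section 3.15 is more cautious and introduces the indicators as a way "to explore the extent to which care activities are aligned with promoting patient independence".

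Section 3.5 makes documentation part of the intervention cycle: "Care decisions and interventions are subsequently documented in the electronic nursing record using the Omaha System classification, generating data on nursing care delivery and patient" (the sentence ends by naming patients' functioning). The dashboard then shows trends in independence scores together with "frequency and types of nursing interventions aimed at supporting independence, individual patient trajectories, and team-level patterns in care delivery". Section 3.10 has intervention teams review it in monthly reflection sessions. Under 3.11, control teams receive no e-learning, preparatory tool, dashboard training or dashboard access.

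Section 3.13 calls the effectiveness outcomes exploratory, with no hypothesis tests. Section 4.2 nevertheless plans effect sizes and confidence intervals to inform a future effectiveness trial. The limitations in 5.1 cover selection bias, social desirability in self-reported fidelity and the different TOPICS-SF channels. They do not cover the record indicators.

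**The concern.** An outcome compared between arms needs the same measuring process in both. Here the record is both the measuring instrument and a target of the intervention. Intervention teams are trained in goal-oriented conversations, document the results, and see what they have documented every month. Control teams do none of this as part of the study. Teams delivering or not delivering this intervention must know their arm, although the article does not discuss blinding.

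A difference on indicators (1) to (3) could thus come from more complete recording, from classifying interventions differently, from scoring needs differently, or from setting different targets, with functioning unchanged. Under the present label it would be reported as preliminary effectiveness, and its effect size would be available for planning the next trial.

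**Working it through.** **Does the measuring process differ by arm?**

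| Step | Intervention arm | Control arm |
|---|---|---|
| Goal conversation | Trained stepwise model plus preparatory tool (3.10) | Usual care (3.11) |
| Documentation | A step of the intervention cycle (3.5) | Routine |
| Feedback of recorded interventions and scores | Monthly, by dashboard (3.5, 3.10) | None (3.11) |
| Source of indicators (1) to (3) | Electronic nursing record (3.15) | Electronic nursing record (3.15) |

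The overlap with the dashboard is explicit for indicator (1), since recorded independence-supporting interventions are displayed. For indicator (2), independence scores are displayed; the article does not say whether they are the same as the care-need scores. For indicator (3), display of scores is stated and display of targets is not.

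**The plan's own numbers.** With 14 teams in total (abstract) and 30 older adults per team (3.17), 14 × 30 = 420. Then 420 × 0.50 = 210 and 420 × 0.70 = 294, which reproduces the stated 210–294. By arm: 8 × 30 × 0.50 = 120 to 8 × 30 × 0.70 = 168 intervention, and 6 × 30 × 0.50 = 90 to 6 × 30 × 0.70 = 126 control.

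The documents give no recording rates or achievement rates. Everything below is illustration with assumed inputs.

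**Indicator (1).** Let q be the true share of delivered interventions that are independence-directed, c the fraction of those recorded, and d the fraction of the others recorded. The indicator reads qc / [qc + (1 − q)d]. Take q = 0.4 in both arms, so care is identical.

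- Independence-directed recording differs (control c = 0.6, intervention c = 0.8, d = 0.9 in both). Control: 0.24 / (0.24 + 0.54) = 30.8%. Intervention: 0.32 / (0.32 + 0.54) = 37.2%. Difference +6.4 points.
- Recording of the others differs (c = 0.8 in both, control d = 0.6, intervention d = 0.9). Control: 0.32 / (0.32 + 0.36) = 47.1%. Intervention: 0.32 / (0.32 + 0.54) = 37.2%. Difference −9.8 points.
- Both recorded more fully by the same factor k: k cancels and the difference is 0.

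**Indicator (3).** Let p be true achievement, equal in both arms, and assume 0.30 to 0.50. Let s, assumed 0.10 to 0.30, be the share whose achievement status changes because targets in the intervention arm are set differently.

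- Easier targets turn a share s of non-achievers into achievers: +(1 − p)s, from 0.50 × 0.10 = 5 points to 0.70 × 0.30 = 21 points.
- More ambitious targets turn a share s of achievers into non-achievers: −ps, from 0.30 × 0.10 = 3 points to 0.50 × 0.30 = 15 points.

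**Scale.** For a proportion of older adults, the 95% half-width of a difference is 1.96 × √[p(1 − p)(1/n₁ + 1/n₂)].

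- With 120 and 90, p = 0.5: 1.96 × √[0.25 × (1/120 + 1/90)] = 13.7 points.
- With 168 and 126, p = 0.3: 1.96 × √[0.21 × (1/168 + 1/126)] = 10.6 points.
- With an assumed intracluster correlation of 0.05, the design effect is 1 + 14 × 0.05 = 1.70 (15 per team) or 1 + 20 × 0.05 = 2.00 (21 per team). The half-widths become 13.7 × √1.70 = 17.8 and 10.6 × √2.00 = 15.0 points.

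The artefact on indicator (3) can therefore be as large as the uncertainty of the comparison, and a larger sample would not remove it. The half-width does not carry over to indicator (1), whose unit is the intervention.

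**The case against.** The strongest reply is that 3.15 presents these indicators as alignment of care activities, within its paragraph on care delivery, and that 4.2 lists the outcome as nursing care delivery patterns. On that view indicator (1) is already a process measure. This largely stands for indicator (1) and makes part of the point a mismatch of wording. It does not remove the effectiveness label that opens 3.15 or the abstract's statement that record data measure independent functioning.

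The outcomes are also exploratory, untested, described only and triangulated with qualitative data (3.13, 4.2, 4.3). This stands and limits the severity. The effect sizes are still meant to inform the next trial.

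Several stronger readings are tempting, but the documents do not support them:

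- A reader might infer that the bias must favour the intervention. The direction is open: proportional gains in recording leave indicator (1) unchanged, and shared goal-setting could produce harder targets as well as easier ones.
- A reader might infer that nurses alone set the targets, or adjust them after seeing them on the dashboard. The article says only that targets are individually set, and does not say that the dashboard displays them.
- A reader might take from the Background that the participating organizations' records are nearly empty, because it reports that "the documentation and evaluation of nursing interventions and patient outcomes remain largely absent, limiting nurses' ability to use data for decision-making". That sentence summarises a review of digital systems in nursing generally and gives no completeness figure for these four organizations.
- A reader might limit the problem to indicators (1) and (3). Indicator (2) comes from the same record and the same teams.

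Rules for dating and revising targets may also stand in a fuller document, so their absence from the article is not itself the fault.

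**Conclusion.** The point holds for all three indicators. The process that produces these data differs by arm because of the intervention itself, and the article both labels the results preliminary effectiveness and omits the problem from its limitations. A between-group difference on them cannot be attributed to independence.

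That conclusion rests on 3.5, 3.10, 3.11 and 3.15, plus one inference: that teams know their arm. It does not rest on the illustrative figures, which show only that a difference of several points in either direction is possible without any change in care or functioning. The true direction and size are unknown. Severity is minor to moderate: no test or decision rule depends on these outcomes, but their effect sizes may feed the design of the next trial.

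**What to change.** 1. In 3.15, classify indicator (1) as a care-process or documentation measure, and bring the abstract into line with 3.15's wording on alignment of care activities.
2. From the extract already planned, report by arm the numbers per older adult of documented interventions, care needs with a target score, and evaluations, beside all three proportions.
3. For indicator (3), report achievement of the first recorded target in both arms, and show targets revised later separately where the record holds dates. Do not restrict to targets set at or before baseline. Table 1 puts the preparatory tool and baseline at the same time point, so targets arising from the shared conversation may be recorded afterwards, and such a cut could drop them more in one arm. The first-target rule makes the handling of revisions equal; it does not make target-setting itself equal.
4. In 5.1, state that indicators (1) to (3) are recorded by teams aware of their arm and are directly affected by the intervention, and that their effect sizes will not be used as evidence of improved independence when the next trial is planned.
5. Do not make their interpretation depend on agreement with TOPICS-SF. Its administration also differs by arm (3.15, 5.1), so it is not a clean check.

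The cost is slightly more extraction work (counts, and dates where they exist) and some wording. The indicators lose their effectiveness label. Whether the records hold target-revision dates is an assumption to confirm.
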